## Abstract

**Background:**

There are an estimated three million people in the United Kingdom with chronic obstructive pulmonary disease (COPD), and the incidence of bronchiectasis is estimated at around 0.1% but is more common in COPD and severe asthma. Both COPD and bronchiectasis are characterized by exacerbations in which bacteria play a central role. Pseudomonas aeruginosa is isolated from sputum samples from 4% to 15% of adults with COPD and is more likely to be isolated from patients with severe disease. Earlier detection of exacerbations may improve morbidity and mortality by expediting treatment. Aseptika Ltd has developed a system for patients to self-monitor important physiological measurements including levels of physical activity, peak flow, forced expiratory volume (FEV1), and biomarkers for P aeruginosa in sputum.

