### Primary and Secondary Endpoints and Outcome Measures

#### Primary Endpoint

An exacerbation will be defined as the initiation of antimicrobial therapy for respiratory symptoms either at home or on admission, with or without concomitant steroids or admission. For participants who are already on continuous antibiotics, an exacerbation will be defined as starting a course of different antibiotics or increasing the dose or frequency of existing antibiotics due to increased symptoms.

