#### Participant and Carer Training

Volunteers will be trained by a research nurse and Aseptika personnel during a visit to the participant’s home. A home visit will clarify which 3G cellular network is available in their location (for Internet access) and will ensure that the participant has space to install a small dedicated freezer and that there is access for delivery.

Each participant will be provided with the following items and participant and carer will be trained on their use:

Physical activity tracker: this will be set up for them and they will be shown how and when to wear it.Smart scale: the participant will be instructed how to weigh themselves and how this measures their body composition (they will be instructed to perform this in bare feet).Blood pressure cuff: the participant will be instructed how to take their own blood pressure and what the results mean.Pulse oximeter: the use of a pulse oximeter and how it works will be explained.Thermometer: the participant will be provided with a noncontact infrared thermometer and will be shown how to take their temperature.Peak flow meter: participants will be shown by the research nurse how to measure their peak flow and FEV_1_ using a simple, automated device.Sputum and urine samples: participant will be taught how and when to take a sample and how to store the sample in the containers provided in the freezer that will be supplied.iPad mini and questionnaires: participant will be trained on how to charge the iPad mini, how to switch it on and off, etc. A short questionnaire about symptoms, medications, and health care usage will be completed on the iPad mini using colorful self-explanatory series of screens within the Activ8rlives App. The display will be brightly colored, and any text (which will be kept to a minimum) will be large in size.

Participants will be able to use the iPad mini for personal use as well as for daily study use within the limits specified and agreed to in the participant consent form. Participants will be requested to take this equipment with them to the hospital if they are admitted and to continue recording these data in the hospital. Initial training will take approximately 60 minutes.

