#### Analysis of Endpoints

The first stage of the data analysis is to use data on the collected parameters (eg, peak flow, pulse rate, oxygen saturation, activity data) to predict when an exacerbation is likely. Control charts will be used to determine the boundaries of normal behavior for each parameter. Separate control charts will be used for each participant, as what constitutes normal behavior will vary from participant to participant. When a parameter strays from normal behavior (eg, exceeds 99% control limits), an exacerbation will be predicted.

To examine the association between predicted exacerbation and actual exacerbation, participant follow-up will be divided into periods of time (eg, 7-10 days). A comparison of actual exacerbation when exacerbation has and has not been predicted will be made. To allow for the repeat measurements over time from the same participants, the analysis will be performed using multilevel logistic regression. Additionally, the sensitivity and positive predictive value of the predictions will also be calculated. Estimated values will be presented along with corresponding confidence intervals. Further exploratory analysis using novel computing methods will be conducted.

Health care use data will be presented descriptively (eg, the frequency and type of health care contacts over the study period for different participant groups).

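### The stated performance measures carry no lead time, so an alarm raised after symptoms began, or under same-period matching even after antibiotics started, can score as a prediction

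*Protocol article*

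**What the plan says.** **Event.** The Primary Endpoint section reads "An exacerbation will be defined as the initiation of antimicrobial therapy for respiratory symptoms either at home or on admission". For participants already on continuous antibiotics, the event is "starting a course of different antibiotics or increasing the dose or frequency of existing antibiotics due to increased symptoms". Both definitions date the event at a treatment decision made because of symptoms. No separate date of symptom onset is defined.

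**Prediction rule.** Analysis of Endpoints sets individual control charts and states: "When a parameter strays from normal behavior (eg, exceeds 99% control limits), an exacerbation will be predicted".

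**Comparison.** The same section divides follow-up into periods of roughly 7 to 10 days and says: "A comparison of actual exacerbation when exacerbation has and has not been predicted will be made". The method is multilevel logistic regression. It continues: "Additionally, the sensitivity and positive predictive value of the predictions will also be calculated". No minimum interval, horizon or alarm-to-event time is mentioned.

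**Purpose.** The Abstract gives the rationale as "Earlier detection of exacerbations may improve morbidity and mortality by expediting treatment". The Primary Objective is to build models that predict an exacerbation, with symptom data among the inputs.

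**Data at hand.** Participant and Carer Training says "A short questionnaire about symptoms, medications, and health care usage will be completed on the iPad mini", and the Abstract lists symptoms among the daily data. Under Data Management, the start of antimicrobial therapy is entered into the same system as the telemetry.

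**The concern.** Usual care at this centre teaches patients to recognise an exacerbation and treat it themselves at home. A monitor adds warning to the extent that it alarms ahead of that. Because the event is the start of treatment for symptoms, there is an interval, of a length the documents do not give, in which the patient is already unwell but no event has yet been recorded. An alarm in that interval may only confirm what the patient has noticed, yet nothing in the odds ratio, sensitivity or positive predictive value sets it apart from an alarm several days before any symptom.

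The period-based comparison adds a second problem. If a period counts as correctly predicted whenever it contains both an alarm and an event, the order of the two within the period plays no part.

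At stake is how the main result is read. A high sensitivity could be taken as evidence of earlier detection when the measure contains no information on timing.

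**Working it through.** **1. The plan's own figures.** Inputs from Sampling and Sample Size: 60% of predicted periods contain an exacerbation, 10% of unpredicted periods do, 1 period in 12 is predicted, 5% significance, 90% power. A two-sided, continuity-corrected comparison of two proportions with allocation 1:11 gives 10 + 110 = 120 periods, as stated. The design effect is 1 + (12 − 1) × 0.18 = 2.98, about 3. Then 120 × 3 = 360 periods, and 360 / 12 = 30 participants. The calculation reproduces.

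**2. What those figures imply.** Of 360 periods, 30 are predicted and 330 are not. Expected exacerbations are 30 × 0.60 + 330 × 0.10 = 18 + 33 = 51.

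- Sensitivity: 18 / 51 = 35%.
- Positive predictive value: 60%.
- Odds ratio: (0.6/0.4) / (0.1/0.9) = 13.5.

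No input is a time in days. These values would be the same whether alarms came a week early or on the day of treatment.

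**3. How period matching treats timing.** Assume fixed periods of W days, antibiotic start equally likely on any day of the period, and an alarm d days away from it. The alarm falls in the same period with probability (W − d)/W, and this is the same whether it comes before or after antibiotic start. It falls in the period before the event's, so that next-period pairing credits it, with probability d/W, and only if it came first.

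| Distance d | Same period, W = 10 (before or after) | Same period, W = 7 (before or after) | Next-period pairing, W = 10 (before only) |
|---|---|---|---|
| 1 day | 90% | 86% | 10% |
| 3 days | 70% | 57% | 30% |
| 7 days | 30% | 0% | 70% |

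The two pairings give opposite rankings of early and late alarms. Sampling and Sample Size compares periods with and without a prediction, which suggests same-period matching. Its next sentence speaks of exacerbation coming after biomarker detection, which suggests an order. Analysis of Endpoints settles neither.

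**4. Illustration on the planned measures.** This is a simulation of 360 ten-day periods with same-period matching and the implied event rate of 51/360. Assumed, not taken from the documents: 80% of events raise an alarm, 3% of periods have a background alarm, and there is no clustering by participant.

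| Timing of alarm | Sensitivity | Positive predictive value | Odds ratio |
|---|---|---|---|
| 0–2 days before antibiotics | 73% | 75% | about 64 |
| 1–3 days after antibiotics | 66% | 67% | about 35 |
| 5–8 days before antibiotics | 35% | 36% | about 5 |

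Under these assumptions all three measures rate an alarm that comes after treatment above one that comes most of a week ahead. The figures show the direction of the problem under one pairing. They do not estimate it for this study.

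**The case against.** Several points on the other side stand.

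- **Antibiotic start is a legitimate reference.** The stated benefit is faster treatment, and an alarm before antibiotics is earlier than treatment under usual care. The Primary Objective is prediction of an exacerbation, with symptoms as an intended input, so some alarms after symptom onset are there by design. A lead over first symptoms is a stricter standard than the document sets.
- **The article is condensed.** It refers to a statistical analysis plan that is not shown. That plan may fix the pairing and the horizon, and the sample-size wording about exacerbation following detection hints at an intended order. This weakens any claim that late alarms will be counted. It does not change the fact that the measures the article does name contain no timing.
- **The gap may be short.** Patients hold antibiotics at home and are encouraged to begin them at once. Reporting lead time would show whether this is so.

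Three stronger readings are tempting but unsupported. A reader might infer that the study cannot show earlier detection. Symptoms, telemetry and antibiotic starts are recorded by day, so the intervals can be derived. A reader might infer that every alarm between symptom onset and treatment is credited. That depends on the unstated pairing, and neither pairing in the working credits all of them. A reader might infer that longer treatment delay makes the system look better. Under same-period matching, an alarm further from antibiotic start is less likely to share its period, which works the other way.

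A reader might also try to size the bias by assuming a daily alarm probability and a treatment delay, and comparing the result with the implied 35% sensitivity. The documents give neither input, and 35% is a per-period planning value, not a target or a result.

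**Conclusion.** The point holds in limited form. The event is dated at a treatment decision that comes with or after symptoms, and the performance measures named in the article do not show whether an alarm preceded the patient's own symptoms. Under same-period matching, even an alarm after antibiotic start could count: in a 10-day period, one day late is credited as often as one day early. The stated analysis therefore does not demonstrate earlier detection. This is a gap in the analysis as described, not in the data or in the event definition.

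The same-period percentages rest on fixed periods and a uniformly placed event, and on a pairing the article suggests but does not fix. The simulated values rest further on assumed alarm rates. The size of any bias in this study cannot be given. The change is worth making because it answers the study's own rationale at little cost.

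**What to change.** 1. Keep antibiotic start, or change of antibiotics, as the event.
2. Count as predictions only alarms that precede the event, within a horizon stated in advance. State how a reading on the same day as antibiotic start is handled.
3. Report the distribution of lead time, in days from alarm to antibiotic start, beside the odds ratio, sensitivity and positive predictive value.
4. As a secondary analysis, for telemetry and biomarker alarms only, date symptom worsening from the daily questionnaire. Use a prespecified rule relative to each participant's own baseline, applied blind to telemetry and biomarkers. Report sensitivity before and after that date separately. Symptom-driven alarms are left out because they would be judged against themselves.

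**Cost.** No new data are needed; the work is derivation and wording. Episodes with missing diary days, or with chronic symptoms and no clear worsening, cannot be dated and must be counted and shown as such. The Results section says the study is already in data analysis, so the rules should be written down before alarms are linked to events and documented under the article's procedure for deviations. If that linkage has already been made, the new results should be labelled post hoc.

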#### Secondary Endpoints

Treatment efficacy will be defined as the day at which antibiotic treatment for that episode is completed.

### Study Participants

#### Inclusion Criteria

The participant must meet all of the following criteria to be considered eligible for the study:

Male or female, aged 18 years or aboveDiagnosed with at least one (or a combination) of COPD and non-CF bronchiectasisTwo or more exacerbations with the same pathogen (*P aeruginosa* or *H influenzae*) proven on culture and treated with antibiotics within the last 12 months, one of which must have been within the last 6 monthsExacerbation-free for the previous 4 weeksProducing at least 1 mL of sputum dailyMust be capable of operating the self-monitoring devices and tablet-based IT system or have a carer capable of undertaking the measurements and collection, storage, and transport of samplesWilling and able to give informed consent for participation in the study

#### Exclusion Criteria

The participant may not enter the study if any of the following apply:

Suspected or confirmed diagnosis of CFAny condition likely to limit participant survival or adherence during the study period in the judgement of the clinician (eg, malignancy, cirrhosis of the liver)Currently taking part in any other research study

Carers will also be included in the qualitative interview and to aid participants with data upload. A carer in this study is defined as an adult (18 years or older) relative or friend who has frequent contact with the participant and will assist the participant to perform measurements or use the iPad tablet to upload data.

### Sampling and Sample Size

Using the sputum biomarkers to predict exacerbations, we based the sample size on the difference in exacerbation frequency in time periods when an exacerbation was predicted compared to time periods when no exacerbation was predicted. This will give an odds ratio of exacerbation following detection of sputum biomarkers.

Time periods will consist of approximately 10 days, of which it will be estimated that there may be on average 12 per participant (assuming an average of 4 months of follow-up). It is estimated that an exacerbation will occur in 60% of time periods in which it is predicted and 10% of time periods in which it is not predicted. It is also assumed that a predicted exacerbation will be made in only 1 in 12 time points (8% of all time points). Using a 5% significance level and 90% power, it is calculated a total of 120 time periods will be required.

However, as there are multiple time periods from the same participant, the data values are unlikely to be independent of each other and thus the sample size requires inflating. Assuming intraclass correlation of 0.18, a design effect of approximately 3 is calculated. This implies that 360 time periods are required for the analysis. This equates to a total of 30 participants for the study. The proposed 30 participants will consist of 20 participants with chronic *P aeruginosa* infection (10 with primarily COPD and 10 with NCFB) and 10 participants with *H influenzae* infection.

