**Objective:**

We aim to test this system in 20 participants with *P aeruginosa* colonization and 10 controls with *Haemophilus influenzae*.

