### Data Analysis

#### Description of Analysis Populations

The study is a nonrandomised cohort of a single group of patients. All subjects recruited into the study will be included in the data analysis.

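### The sample size for the P aeruginosa biomarker odds ratio counts 120 periods from 10 H influenzae controls, so the stated 360 periods and 90% power do not describe the P aeruginosa analysis

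*Protocol article*

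**What the plan says.** Sampling and Sample Size names the predictor that was powered: "Using the sputum biomarkers to predict exacerbations, we based the sample size on the difference in exacerbation frequency", comparing periods with and without a prediction, and "This will give an odds ratio of exacerbation following detection of sputum biomarkers". The biomarkers are described in the Introduction as markers of P aeruginosa virulence, and the Primary Objective is to predict a P aeruginosa exacerbation.

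The first planning assumption reads "an exacerbation will occur in 60% of time periods in which it is predicted and 10% of time periods in which it is not predicted"; the second is that "a predicted exacerbation will be made in only 1 in 12 time points (8% of all time points"). From these, "Using a 5% significance level and 90% power, it is calculated a total of 120 time periods will be required". An intraclass correlation of 0.18 with about 12 periods per participant gives a design effect of about 3, and then "This implies that 360 time periods are required for the analysis", which the section equates to 30 participants. It fills the 30 with 20 P aeruginosa and 10 H influenzae participants.

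The Abstract's Objective gives the second group its role: 20 participants with P aeruginosa colonization "and 10 controls with" H influenzae. Description of Analysis Populations calls the cohort a single group and adds: "All subjects recruited into the study will be included in the data analysis". Analysis of Endpoints describes one multilevel logistic regression and mentions no pathogen term, stratum or restriction. Participant groups appear there only for the descriptive health care use data.

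**The concern.** The calculation is for one question, whether a P aeruginosa sputum marker predicts exacerbation, but a third of the periods counted towards it come from participants enrolled as controls because they have a different pathogen.

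Either reading causes a problem. If the controls are left out of the biomarker odds ratio, the 360 periods are not reached at the planned 12 per participant. If they are included, the 360 is reached with people outside the target of the marker. Their periods would fall mainly in the not-predicted category, and their exacerbations would count as misses for a marker that was not expected to flag them. The odds ratio would then partly reflect any difference in exacerbation rate between the two infection groups. A separate analysis plan could choose between these readings. It could not make the 360 in the sample size section describe the P aeruginosa participants alone.

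**Working it through.** **Inputs** (all from Sampling and Sample Size): exacerbation in 60% of predicted and 10% of unpredicted periods; predictions in 1 of 12 periods, so a ratio of 1:11; 5% significance (taken as two-sided, because that reproduces the plan's figure); 90% power; 12 periods per participant; intraclass correlation 0.18.

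**1. Reproduce the plan.** Pooled proportion = (0.6 + 11 × 0.1)/12 = 0.1417, with variance 0.1417 × 0.8583 = 0.1216.
- Uncorrected number of predicted periods: [1.96 × √(0.1216 × 12/11) + 1.2816 × √(0.24 + 0.09/11)]² / 0.5² = (0.714 + 0.638)²/0.25 = 7.31.
- With continuity correction: (7.31/4) × [1 + √(1 + 2 × 12/(7.31 × 11 × 0.5))]² = 9.37, rounded up to 10. Total 10 × 12 = 120, an exact match. The uncorrected two-sided formula gives 96, so it is not the one used.
- Design effect: 1 + 11 × 0.18 = 2.98. Then 120 × 2.98 = 357.6, or 360 with a design effect of 3; 360/12 = 30 participants.

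The chain is arithmetically correct. The question is who is counted.

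**2. P aeruginosa participants only.** 20 × 12 = 240 periods; the controls supply the other 10 × 12 = 120. Effective periods: 240/2.98 = 80.5, of which 80.5/12 = 6.71 are predicted and 73.8 are not.

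Continuity-corrected power = Φ[(d − a)/b], where:
- d = 0.5 − 0.5 × (1/6.71 + 1/73.8) = 0.419
- a = 1.96 × √(0.1216 × (1/6.71 + 1/73.8)) = 0.276
- b = √(0.24/6.71 + 0.09/73.8) = 0.192

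This gives Φ(0.74) = 0.77.

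| Method, 240 periods | Power |
|---|---|
| Continuity-corrected (reproduces the plan's 120) | 77% |
| Fisher exact, 6 v 74 to 7 v 73 | 77% to 82% |
| Log odds ratio | 84% |
| Unpooled | 74% |
| Pooled, uncorrected | 88% |

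The continuity-corrected method gives 92% at the full 360 periods; the excess over 90% comes from rounding 9.37 up to 10.

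**3. Full six months.** With 18 ten-day periods each, 20 × 18 = 360. The same design effect formula becomes 1 + 17 × 0.18 = 4.06, leaving 360/4.06 = 88.7 effective periods: power 81% corrected, 90% uncorrected.

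**4. Is the design effect right for this comparison?** 1 + (m − 1) × ICC fits an exposure that is constant within a participant. Here predicted and unpredicted periods occur in the same participant, so much of the between-participant variation cancels. A simulation with 20 participants × 12 periods, alarms in 1 of 12 periods varying within participants, a random intercept with ICC 0.18 on the latent scale (an assumption; the article does not give the scale), marginal rates of 60% and 10%, and exchangeable GEE with bias-reduced errors gave power of about 99%. It assumes the alarm chance is the same in every participant. If alarms concentrate in a few participants, the design effect moves back towards 2.98.

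**5. Effect of pooling.** Among the 20: 20 alarm periods with 12 exacerbations, and 220 others with 22. Odds ratio = (12/8)/(22/198) = 13.5; sensitivity = 12/34 = 35%. Add 120 control periods, assuming no control alarms:

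| Assumed control rate | Unpredicted periods with / without exacerbation | Odds ratio | Sensitivity |
|---|---|---|---|
| 5% | 28 / 312 | 16.7 | 12/40 = 30% |
| 10% | 34 / 306 | 13.5 | 12/46 = 26% |
| 14% | 38.8 / 301.2 | 11.6 | 12/50.8 = 24% |

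The article gives no control rate, so these rows are illustrations.

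**The case against.** The strongest reply is that no power is really lost. The 77% depends on a design effect that does not suit the comparison, and a calculation that respects the within-participant alarm puts the 20 participants well above 90%. That stands. A reader might infer from the 240 periods that the study is underpowered or needs more P aeruginosa participants. The documents do not support that: the shortfall exists only inside the plan's own derivation.

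A second reply is that the H influenzae participants belong in the primary analysis. The Primary Objective combines biomarkers with telemetry and symptoms, Analysis of Endpoints gives peak flow, pulse rate, oxygen saturation and activity as examples of alarm parameters, and the endpoint is any respiratory exacerbation treated with antimicrobials, whatever the pathogen. This is correct for telemetry and symptom models, where these participants can contribute both alarms and events. It does not reach the sputum biomarker odds ratio, which is what the sample size section says it powers.

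Third, pooling in the biomarker model is an inference. Including everyone in the data analysis is not the same as fitting one unstratified biomarker model, and a fuller plan may separate the groups. A reader might infer that the controls have lost their purpose or that the odds ratio will be biased. The text does not establish either, and at a 10% control rate the odds ratio does not move. What stands against this reply is that separating the groups would leave the stated 360 unmet at 12 periods each.

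Finally, this is not an arithmetic error, since 120, 360 and 30 follow from the inputs.

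**Conclusion.** The concern holds as a fault in the stated basis of the sample size and in the definition of the analysis set. The 360 periods include 120 from controls who are outside the target of the biomarker being powered. For the 20 P aeruginosa participants, the plan's method supports about 77% power rather than 90%, with a range of 74% to 88% across two-sided formulas at 12 periods each, and about 81% (corrected) at 18 periods each.

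These figures take the plan's rates, alarm frequency, ICC and design effect formula as given. Under the assumptions of the within-participant simulation, the true power for 20 participants is comfortably above 90%, so a claim that the study cannot deliver 90% power would go too far.

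Pooling the controls into the biomarker model would lower apparent sensitivity whenever controls exacerbate without a biomarker alarm. It would shift the odds ratio only if their rate differs from 10%: from 13.5 to between 16.7 and 11.6 for assumed rates of 5% to 14% with no control alarms. Severity is moderate.

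**What to change.** - In Sampling and Sample Size and in Description of Analysis Populations, name the 20 P aeruginosa participants as the primary set for the biomarker analysis.
- State the role of the 10 H influenzae participants: a negative control for the biomarker (false-alarm rate, and a group-by-alarm comparison) and contributors to the telemetry and symptom models.
- Keep the pooled 30-participant analysis as secondary.
- Restate power for 240 periods, either as about 77% by the existing method or as a figure from a within-participant simulation, giving the ICC scale, the alarm distribution across participants and the analysis model.

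The article's Results section says that data analysis is under way, so the analysis set should be fixed and recorded under the article's own provision for documenting deviations before results are reported.

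The cost is rewording, one recalculation and a small added analysis. No extra participants are needed. The drawback is a less favourable power statement, or one that has to be re-derived.
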